### ***B.3. Methods***

This study is designed as a community-based health intervention trial. A key feature of such trials is the allocation of intact communities or clusters of individuals rather than individuals themselves to intervention or control groups [23].

[figure not shown]

### ***B.3.1. Interventions, participants and participating areas***

Two different interventions will be developed, one of them meant to increase awareness and attendance among users (WP1), and the other one targeting health professionals (WP2).

#### ***WP1- User intervention***

##### ***Assessment previous to the development of the intervention (Timeline 2017/1)***

Our approach to the development of the intervention follows the consensus in the field of immigrant health on the need to involve minority ethnic communities in the research process and to support them to define appropriate participatory practices for themselves. Participatory approaches that empower people from these populations, both to define research questions, identify effective interventions and define best practice are considered important to making studies meaningful and effective for tackling inequalities [24]. Thus, the User intervention will be developed based on a) existing literature, b) results from analyses of use of primary care services for screening purposes among immigrants previous to the intervention conducted newly by the study group [2] and c) preliminary interviews with the users (women from Somalia and Pakistan).

Through focus group (FGD) and in-depth interviews including approximately 50 women from Pakistan and Somalia we will explore 1) factors responsible for the low participation rate in the screening program by immigrant women; 2) women's own thoughts about participation in the screening program and how they can help to increase the participation; 3) preferred type of intervention to raise their awareness and participation rate. The participants will be recruited using a maximum variation sampling aimed at diversity in terms of education, age, and number of years lived in Norway. Six to eight FGDs, with each FGD involving six women will be conducted from the two communities separately. Pre-trained females from the communities who are well connected and integrated into local communities will do the recruitment from Pakistan and Somalia.

#### ***Participants***

Women from Somalia and Pakistan are chosen as targets for the *User intervention* following demographic patterns and earlier analyses [2]. All women from these countries living in the intervention areas compose the intervention groups; immigrant women from the same countries of origin living in control areas will be control participants. It is conservatively estimated that 625 and 915 women in screening age from Somalia and Pakistan respectively live in the study area. Approximately half of each part of the women from each country will live in the intervention clusters and will be invited to the study by the bilingual key women through different channels (invitation through the mosque in collaboration with local stakeholders, information at the local shopping centres, snow-ball oral information, etc).

### Area and sample size

This intervention will be implemented in Akershus and Buskerud. These counties are chosen based on the existence of enough immigrants but avoiding areas known to have low participation rates due to on-going research programs in other health fields. Sample size is calculated for an increase in cancer screening participation from 0.45 to 0.55 with 80% power and 5% significance level. After trying several intra class correlation (ICC) levels, we decided to divide four municipalities in Akershus and Buskerud (Asker, Bærum, Lørenskog and Drammen) in 16 clusters that were matched according to the calculated number of female immigrants aged 20 to 66 from Somalia and Pakistan. To avoid contamination, after assuring that pairs were not naturally linked by a mosque or other natural known gather centre for these populations, clusters will be randomly assigned to intervention or control groups (matched pair randomization) [25].

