#### **A.2.1 The Norwegian Cervical Cancer Screening Program**

The Norwegian Cervical Cancer Screening Program (NCCSP) aims to reduce the incidence and mortality of cervical cancer through identifying and treating early cancer stages, which if left untreated have a high likelihood of progressing to invasive cancer. It was implemented in 1995, and it is based on triennial screening with cytology smears among women aged 25-69. Women with no registered screening test during the last three years receive a reminder letter from the Norwegian Cancer Register with a recommendation to make an appointment with their general Practitioner (GP) to have a smear. Overall, 76% of the women have taken a smear after two reminders [11]. While the letters and reminders raise the attendance for the general population, their effectiveness among immigrants is unknown. The screening programme in Norway does not explicitly target immigrant women and hence they are usually under-recruited and not represented at the population level. Yet another constraint is that the reminders are sent in Norwegian, which might dissuade immigrant women from participating in screening or health intervention programmes. According to the Cancer Registry of Norway, more than half of the women diagnosed with cervical cancer have rarely or never taken a Pap test. The NCCSP is changing the test stepwise in Norway, but the type of test taken by the health professional will not affect the results of our study.

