#### **1. Data from linked national registers**

To avoid the shortcomings of self-reports, outcome information on screening attendance for intervention and controls used for all WPs will be obtained from the Norwegian Cervical Cancer Screening Program, where all pap smears taken in Norway are registered. The leader of this Register is part of the Reference group for this study. From this Register we will apply for information on women who have taken a test, if it is normal or pathological as well as the date for test for all women in Norway. This information will be linked at the individual level to the Norwegian National Registry including information regarding immigrant background (country of origin, reason for migration and length of stay in Norway) for all 25 to 69 years

old registered in Norway, in addition to other socioeconomic variables (age, education, income level, work status, cluster area for those in intervention and control areas, geographical centrality, civil status, husbands' immigrant background and GP's immigrant background) that will be used to adjust our results. Last, a link of the individual woman to his or her GP will be possible through the GP database (Fastlegedatabase) that also includes GP's age and gender. Information will be linked by Statistics Norway, and data will be stored in a secure server at the University of Bergen (BIOS, Core Facility for Biostatistics and Data Analyses) in an anonymised form available only for the study researchers. The Western Regional Committee for Medical and Health Research Ethics has already approved the linking of these data.

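### Clusters are matched on women aged 20 to 66, but the programme and the linked outcome data cover ages 25 to 69, so the matching count is not a count of the women to be analysed

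*Protocol*

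**What the plan says.** Four places in the protocol bear on this.

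- *Area and sample size*: four municipalities are divided into 16 clusters, "matched according to the calculated number of female immigrants aged 20 to 66 from Somalia and Pakistan". One cluster of each pair goes to intervention and the other to control. Cluster size is the only matching variable named.
- *A.2.1 The Norwegian Cervical Cancer Screening Program*: "it is based on triennial screening with cytology smears among women aged 25-69".
- *B.3.2 Measurements, Data from linked national registers*: the outcome comes from the screening register, "where all pap smears taken in Norway are registered". It is linked to population data on immigrant background "for all 25 to 69 years" old.
- *Participants*: "It is conservatively estimated that 625 and 915 women in screening age from Somalia and Pakistan respectively live in the study area". No ages are given there. On allocation, the section says: "Approximately half of each part of the women from each country will live in the intervention clusters".

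The protocol does not say why the matching band differs from the programme band.

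**The concern.** Matching on size is meant to give the two clusters of a pair similar numbers of women who will be analysed. Here the size is counted over a band that starts five years too early and stops three years too soon for that purpose. If clusters differ in their share of women aged 20 to 24 or 67 to 69, pairs that look equal on the matching count will be unequal on the analysed count.

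There is a second, conditional issue. The 1,540 women in *Participants* are described as being of screening age but have no age limits attached. If that total comes from the same 20 to 66 tabulation, the description is wrong and the analysable number may be overstated. If it is a 25 to 69 count, the total and the matching describe different populations. Either way the protocol needs one clarification.

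**Working it through.** **Step 1. Compare the bands.**

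- Matching band, 20 to 66: 66 − 20 + 1 = 47 single-year ages.
- Programme and linked data, 25 to 69: 69 − 25 + 1 = 45 single-year ages.
- Shared, 25 to 66: 42.
- Counted but outside the programme band: 20 to 24, 5 of 47 ages (10.6%).
- In the programme band but not counted: 67 to 69, 3 of 45 ages (6.7%).

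These are shares of single-year ages, not of women. The protocol gives no age distribution for Somali and Pakistani women in the study area.

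**Step 2. Check the plan's own design figures.** Stated inputs (*Area and sample size*, *Participants*): attendance 0.45 versus 0.55, 80% power, 5% significance, 16 clusters, 625 + 915 = 1,540 women, about half per arm. Assumed: a two-sided test. Neither a required sample size nor an ICC is stated, so the calculation cannot be reproduced, only tested for consistency.

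- Per arm without clustering: n = [1.96·√(2·0.5·0.5) + 0.8416·√(0.45·0.55 + 0.55·0.45)]² / 0.10² ≈ 392.
- Women per arm: 1,540/2 = 770. Mean cluster size: m = 1,540/16 = 96.25.
- Design effect: DE = 1 + (m − 1)·ICC.
- ICC at which 770 per arm gives 80% power: (770/392 − 1)/(96.25 − 1) = 0.0101.

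The design is therefore consistent with 80% power at an ICC of about 0.01. Power with 1,540 women at other values, from an effective 770/DE per arm:

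| ICC | DE | Power |
|---|---|---|
| 0 | 1.000 | 97.6% |
| 0.005 | 1.476 | 89.9% |
| 0.01 | 1.953 | 80.3% |
| 0.02 | 2.905 | 63.5% |
| 0.05 | 5.763 | 37.2% |

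This approximation ignores any gain from matching and the small number of clusters. It serves to compare sample sizes, not to give a definitive power.

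**Step 3. Effect of the age band, only if 1,540 is a 20 to 66 count.** Assume that 5% to 20% of the women counted are aged 20 to 24, and that women aged 67 to 69 would add back 0% to 6%.

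- Lowest: 1,540 × (1 − 0.20 + 0) = 1,232 women, m = 77.0.
- Highest: 1,540 × (1 − 0.05 + 0.06) ≈ 1,555 women, m = 97.2.

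| ICC (assumed) | 1,540 women | 1,232 women | 1,555 women |
|---|---|---|---|
| 0.005 | 89.9% | 84.9% | 90.1% |
| 0.01 | 80.3% | 75.5% | 80.5% |
| 0.02 | 63.5% | 60.0% | 63.6% |

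At ICC 0.01 the change runs from a loss of 4.8 percentage points to a gain of 0.2.

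**Step 4. If 1,540 is already a 25 to 69 count**, sample size and power do not change, and only the matching variable is affected.

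**The case against.** The strongest reply is that the 20 to 66 band is attached only to the matching count. The sole sample figure is labelled as being of screening age, which the protocol elsewhere sets at 25 to 69, and it is called conservative. On a plain reading, power is untouched. That stands: a reader might infer that the trial was sized on the wrong ages, but the text does not show it.

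A reader might also infer that women aged 20 to 24 can never contribute an outcome. That goes too far. The timeline puts implementation in 2017 and uses register data for 2016 to 2018, so some of them reach 25 within the window. Likewise, some women counted at 64 to 66 move into the omitted ages, and some aged 67 to 69 pass the upper limit. The register itself holds all smears. The accurate statement is that women are outside the linked population while they are under 25.

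Nor can a definite power loss be drawn from the statement in *A.1* that over half of immigrants are aged 20 to 40. That describes immigrants from all countries, not Somali and Pakistani women in four municipalities.

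Finally, a uniform overcount would leave the pairs unchanged, and no cluster-level age data are given. Age is a planned adjustment variable, and attendance from 2012 supplies a baseline. These points limit the harm. They do not explain why the only named matching variable is counted over a different population from the one analysed.

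**Conclusion.** The inconsistency is explicit: matching uses ages 20 to 66, while the programme and linked data use 25 to 69. The likely consequence is modest. Pairs may be less well balanced on analysable women, at some cost in precision. How much cannot be computed without age data by cluster. The randomised comparison is not biased by it.

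Any effect on power depends on 1,540 being a 20 to 66 count, which the protocol leaves open. In that case, at an assumed ICC of 0.01 and the assumed age shares, power is between 75.5% and 80.5%, a range that includes no loss. The unstated ICC matters far more: moving it from 0.005 to 0.02 takes power for the same 1,540 women from 89.9% to 63.5%. The point is worth correcting because the correction is cheap and, on the protocol's wording, randomisation is still to come.

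**What to change.** Before randomising:

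1. Recount women from Somalia and Pakistan aged 25 to 69 in each of the 16 clusters.
2. Re-form the eight pairs on that count.
3. Repeat the check that the paired clusters do not share a mosque or other gathering place, since new pairs may not have been checked.
4. Use one age band in *Participants*, *Area and sample size* and the section on linked registers, and state the ages to which the 625 and 915 refer.

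If allocation has already been made, keep it and report cluster sizes for ages 25 to 69. Restate the sample and power only if 1,540 proves to be a 20 to 66 count.

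The cost is one re-tabulation, a repeat of the check on shared gathering places, and possibly a slightly smaller stated sample.

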### Design and development of the intervention (Timeline 2017/2)

As explained above, we cannot outline the detailed intervention at this point, but based on the existing literature, the possibilities are among others: personal meetings with the women organised according to their practical needs and including the videos, interactive material or written information, etc. The intervention material will be designed and developed in close collaboration with the Norwegian Cancer Society and the NCCSP in order to make it adaptable to the national program in case they prove efficient. We will use professional expertise (communication expert) to develop intervention material.

### Implementation of intervention (Timeline 2017/3)

Bilingual key women (project assistants) from Somalia and Pakistan will be recruited and trained as peer educators for their respective communities to increase awareness regarding the importance of cervical cancer prevention and to help peers overcome detected barriers and increase attendance to screening. Strategies to achieve these goals will be developed as explained above (Timeline 2017/2).

### WP2- Heath professional intervention (not included in this application)

A similar process is being used since 2015 to develop the *Heath professional intervention*, but interviewing health professionals. Bergen was divided into 20 clusters according to the 20 geographical subareas defined by Statistics Norway and similar calculations and matched pair randomization to those described above were conducted. All GPs, midwives and private gynaecologists working in the intervention cluster areas will be assigned to the intervention group; similar health professionals working in the other municipalities will be chosen as controls. This intervention will be implemented in Hordaland (Bergen) in autumn 2016 to increase awareness of the health professionals involved in screening working in the chosen municipalities. No change in “screening as usual” will be implemented for health professionals working in the control areas. Our experience in this process will facilitate work related to WP1.

### **B.3.2 Measurements**

The study will rely on both quantitative and qualitative evaluation of the interventions in addition to health economic evaluation.

#### **1. Data from linked national registers**

To avoid the shortcomings of self-reports, outcome information on screening attendance for intervention and controls used for all WPs will be obtained from the Norwegian Cervical Cancer Screening Program, where all pap smears taken in Norway are registered. The leader of this Register is part of the Reference group for this study. From this Register we will apply for information on women who have taken a test, if it is normal or pathological as well as the date for test for all women in Norway. This information will be linked at the individual level to the Norwegian National Registry including information regarding immigrant background (country of origin, reason for migration and length of stay in Norway) for all 25 to 69 years

old registered in Norway, in addition to other socioeconomic variables (age, education, income level, work status, cluster area for those in intervention and control areas, geographical centrality, civil status, husbands' immigrant background and GP's immigrant background) that will be used to adjust our results. Last, a link of the individual woman to his or her GP will be possible through the GP database (Fastlegedatabase) that also includes GP's age and gender. Information will be linked by Statistics Norway, and data will be stored in a secure server at the University of Bergen (BIOS, Core Facility for Biostatistics and Data Analyses) in an anonymised form available only for the study researchers. The Western Regional Committee for Medical and Health Research Ethics has already approved the linking of these data.

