### ***B.3.3 Other methodological issues***

#### ***a. Secular trends***

Secular trends, or changes through time disregarding intervention can be a challenge in this type of study. As our outcome measurements rely on linking existing databases, we will include an extended baseline period (from 2012) with repeated measurements of screening attendance several years previous to intervention to better determine the influence of secular trends.

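### The protocol lists cluster area as an adjustment variable although it determines the arm, and omits each woman's earlier screening status, which the register extract already holds

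*Protocol*

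**What the plan says.** Under B.3.2, item 1 (data from linked national registers), the protocol names the variables to be linked to the screening data. Among age, education, income, work status and similar items stands "cluster area for those in intervention and control areas, geographical centrality, civil status". The list closes with its purpose: these are variables "that will be used to adjust our results". Nowhere is cluster area described as a random effect, a unit of analysis or a stratum.

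The section on area and sample size divides four municipalities "in 16 clusters that were matched according to the calculated number of female immigrants" from the two countries, and states that "clusters will be randomly assigned to intervention or control groups (matched pair randomization").

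The adjustment list contains no earlier screening variable. The same section nevertheless obtains test results "as well as the date for test for all women in Norway", and says "This information will be linked at the individual level to the Norwegian National Registry". Under B.3.3 a, on secular trends, "we will include an extended baseline period (from 2012) with repeated measurements of screening attendance several years previous to intervention". The only purpose given there is to judge the influence of secular trends.

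**The concern.** Two features of the stated list deserve attention.

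First, every cluster is wholly intervention or wholly control, so arm is an exact sum of cluster indicators. Read in the usual way, beside age and education, adjusting for area means a categorical covariate. In a follow-up comparison that takes up all the information on arm. In a before-after model it does not, but a covariate is no substitute for inference at the level of the randomised unit.

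Second, a woman's own screening record is plausibly a strong predictor of later attendance. Clusters were matched on the number of women only, so eight pairs can differ by chance in baseline attendance. The data to correct for this are already in the extract, but the list does not use them.

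**Working it through.** **Inputs from the protocol.** 16 clusters, taken as 8 matched pairs. Women of screening age: 625 + 915 = 1540, about half in each arm, so 770 per arm and m = 1540/16 = 96.25 per cluster. Planning statement: "Sample size is calculated for an increase in cancer screening participation from 0.45 to 0.55 with 80% power and 5% significance level". Two-sided testing is assumed.

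**Assumptions, not in the protocol.** ICC 0.005 to 0.02; cluster-level correlation between baseline and follow-up (CAC) 0.6 to 0.8; individual-level correlation (IAC) 0.2 to 0.4.

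**The plan's own figure.** Without clustering, n per arm = (1.96·√(2·0.5·0.5) + 0.8416·√(0.45·0.55 + 0.55·0.45))² / 0.10² ≈ 392. The available 770 per arm allow a design effect of 770/392 = 1.96, which corresponds to ICC = (1.96 − 1)/95.25 ≈ 0.010. At ICC 0.01 the normal-approximation power is 0.803. The stated 80% is therefore consistent with an ICC near 0.01. The protocol does not report the ICC it used, so this is not a strict reproduction.

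**Estimability (rank of the design matrix).**

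| Model | Columns | Rank | Arm effect |
|---|---|---|---|
| 16 cluster indicators + arm, follow-up only | 17 | 16 | not estimable |
| 8 pair indicators + arm, follow-up only | 9 | 9 | estimable |
| 16 cluster indicators + period + arm-by-period, before and after | 18 | 18 | estimable |

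**Type I error, follow-up comparison with clustering wholly ignored.** DE = 1 + 95.25·ICC; true error = 2·(1 − Φ(1.96/√DE)).
- ICC 0.005: DE 1.48, error 10.7%.
- ICC 0.01: DE 1.95, error 16.1%.
- ICC 0.02: DE 2.91, error 25.0%.

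**Type I error, before-after model with cluster indicators and individual-level standard errors.** The indicators absorb the stable part of the cluster variance and leave the cluster-by-period part, ICC·(1 − CAC). With separate samples per period the variance is understated by a factor of about 1 + m·ICC·(1 − CAC)/(1 − ICC).

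| ICC | CAC 0.8: factor, error | CAC 0.6: factor, error |
|---|---|---|
| 0.005 | 1.10, 6% | 1.19, 7% |
| 0.01 | 1.19, 7% | 1.39, 10% |
| 0.02 | 1.39, 10% | 1.79, 14% |

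**Gain from a baseline covariate at ICC 0.01.** The correlation of baseline and follow-up cluster means is r = (m·ICC·CAC + (1 − ICC)·IAC)/(1 + (m − 1)·ICC).
- Lower end: (0.9625·0.6 + 0.99·0.2)/1.9525 = 0.40.
- Upper end: (0.9625·0.8 + 0.99·0.4)/1.9525 = 0.60.
- The variance factor 1 − r² is 0.84 to 0.64, a reduction of 16 to 36%.

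The unadjusted standard error is √(2·0.2475·1.9525/770) = 0.0354, so the noncentrality is 0.10/0.0354 = 2.82. With inference on 8 pairs, noncentral t and no credit for matching:
- no baseline covariate, 7 df: power 68%;
- with the baseline covariate, 6 df: noncentrality 3.08 to 3.53, power 73 to 83%.

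**The case against.** The strongest reply is that the protocol commits to no model. The list stands in a section on measurements and data linkage. Cluster area must be in the extract for any cluster-aware analysis, and adjusting can mean a random effect, cluster summaries or robust errors. The protocol describes allocation of intact communities, says several ICC levels were tried and pairs its clusters, so the team knows what the unit is. The model may be set out in a statistical analysis plan that is not at hand. This reply stands to a large extent. What remains is that the protocol does state a use for the variable, and the wording, taken literally, is the wrong use.

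A reader might infer that the listed adjustment removes the treatment effect. That holds only for fixed-effect entry in a follow-up-only comparison. The protocol plans repeated baseline measurements from 2012, and a before-after model with cluster indicators has full rank. An inestimable arm term would also show itself on fitting.

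A reader might attach the 11 to 25% error range to the listed adjustment. It belongs to a follow-up comparison with no cluster term at all. Even 6 to 14% assumes separate samples per period. If the same women are followed and their repeated measurements are treated as independent, IAC of 0.2 to 0.4 brings the error to about 2-5%, 3-7% and 5-12% at ICC 0.005, 0.01 and 0.02, so some cases are conservative.

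On prior screening, leaving out a baseline covariate does not invalidate a randomised comparison. Judging secular trends by arm may also bring in change from baseline, so the documents do not show that imbalance would go uncorrected.

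**Conclusion.** The point holds as a flaw in a stated list, not as a defect that invalidates the trial. Cluster area is listed for a role it cannot serve as a fixed covariate in a follow-up comparison. In a before-after model it leaves the effect estimable, but does not by itself give standard errors at the level of the randomised unit: error is about 6 to 14% under the assumptions above. Omitting each woman's earlier screening status costs precision and control of chance imbalance across eight pairs, not validity.

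The gain from the baseline covariate, 68% to 73-83% power, rests on an assumed ICC of 0.01 and assumed correlations. The same variance reduction in an unpaired analysis would read as 75% (14 df) rising to 81-90% (13 df), but those degrees of freedom do not fit inference on 8 pairs and should not be quoted for it. The change is recommended and cheap. It is not a must-fix, because the protocol fixes no model.

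**What to change.** 1. Take cluster area out of the list of adjustment covariates. State that it is the clustering or analysis unit and that matched pair is the stratum, with inference based on the 8 pairs. A paired cluster-level analysis, or a permutation test over the 2⁸ = 256 within-pair allocations, would do.
2. Add each woman's test status in the three years before her pair's intervention start, with an indicator for women not resident throughout that window, and/or the cluster's baseline attendance.

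The cost is a change of wording and some analysis work. The dated, individually linked tests are already in the planned extract. A cluster-level baseline covariate uses one degree of freedom (7 to 6). If it explained nothing, power in the calculation above would fall from 68% to about 66%.
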